## Discussion

In the UMBRELLA Fit study, we will investigate the feasibility of the cmRCT design in the field of exercise-oncology. In addition, we will estimate the effectiveness of an exercise intervention on the QoL of inactive patients with breast cancer. Previous RCTs in the field of exercise-oncology have shown beneficial effects of physical activity on treatment-related side-effects, for example QoL. However, conventional RCTs in the field of exercise-oncology have several limitations, i.e. contamination, high drop-out in the control group, reduced generalizability, difficult accrual and insight only into the short-term effects. We hypothesized that the cmRCT design might overcome these shortcomings.

We acknowledge that the cmRCT design poses some challenges. A higher rate of drop-out after randomization is expected in the intervention group compared to conventional RCTs. Using intention-to-treat analysis, including all patients regardless of non-compliance and drop-out, might considerably dilute the actual treatment effect. Consequently, important clinical intervention effects might be missed. The estimated intervention effect depends on the proportion of non-compliance and becomes more diluted as non-compliance increases. Since compliance with the regular cohort measurements in the control group is expected to approximate 100% because they will not be informed about the study, the proportion of non-compliance in the control group will be lower when using the cmRCT design compared to a RCT. The lower non-compliance in the control group compensates the higher non-compliance in the intervention group [23].

The instrumental variable method will be used to estimate the intervention effect, taking drop-out/non-compliance after randomization into account. This method uses the random treatment assignment as an instrumental variable to control for non-compliance. However, disadvantage of this method in the cmRCT design is that we only know who will accept and complete the exercise programme in the intervention group, but this information is lacking from the control group. Patients who accept and complete the exercise programme might differ from those who do not. To deal with this lack of information, we will develop a prognostic model to estimate which patients would have been compliant in the control group by using the information on non-compliance of the intervention group.

Another challenge is the dependence on information collected within the cohort for the assessment of eligibility and for the outcome. If the available information is insufficient, there is a possibility that selected participants will not meet the inclusion criteria, e.g. due to severe comorbidity not yet registered in the cohort. However, since randomization has already been executed, these patients stay in the intention-to-treat analyses. In addition, another limitation of dependency on routine measurement outcomes is that the potential cmRCT outcomes are limited to outcome measures already collected in the observational cohort study. There is no opportunity to obtain additional information from the control group by additional measurements or at additional time points.

Patients are enrolled at 12 or 18 months after inclusion in UMBRELLA because at this time most of these patients have finished their primary treatment. In this period, the impact of diagnosis and treatment on normal daily living (e.g. complaints of fatigue, impaired quality of life) become more prominent [3–6]. Because previous research has shown that exercise has a beneficial effect on the QoL of patients with breast cancer in this period, the UMBRELLA Fit study gives the opportunity to assess the feasibility of the cmRCT design in the field of exercise-oncology by comparing the results of this trial with previous exercise trials in patients with breast cancer.

In summary, the UMBRELLA Fit study examines the effects of exercise on the QoL of patients with breast cancer, using the cmRCT design. The purpose of this study is twofold. The first goal is to determine the feasibility of the cmRCT design in the field of exercise-oncology and compare this with conventional RCTs in this field. The second goal is to examine the effectiveness of the exercise intervention on the QoL of patients with breast cancer in the short term (6 months) and long term (24 months).

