### Recruitment and allocation

UMBRELLA participants meeting the inclusion criteria will be randomly allocated to the intervention or control group with a 1:1 ratio, by an independent data manager using a computer-generated randomization list. Randomization will be stratified for time since enrollment (12 or 18 months). Patients randomized to the intervention group will receive an offer by mail to participate in an exercise programme, a patient information sheet and an informed consent form. After 1–2 weeks these patients are contacted by telephone to further explain the study. If patients decide to participate, a last check of eligibility will be performed. Contra-indications to the exercise programme will be screened using the Physical Activity Readiness Questionnaire (PAR-Q) [27]. If eligible, they will be invited to visit the UMC Utrecht to sign the informed consent form for the UMBRELLA Fit study and undertake a baseline assessment. If patients refuse to participate because of bad timing of the invitation, they will be asked if they are willing to start later. Patients randomized to the control group will not be informed about the study. Recruitment started in October 2015.

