Strength training consists of a set of exercises, focusing on all major muscle groups. During the intake session at the physiotherapist centre, 20 repetition maximum (RM) tests will be performed to determine the training load (the maximum weight at which a muscle group can perform 20 repetitions) for the different exercises. These weights will be the starting point for each strength exercise. A 20 RM and 15 RM test will be repeated in the fourth and eight weeks of the programme (Table 1). In the case of physical limitations, the exercise programme will be adapted in consultation with the researchers.

In addition to the supervised exercise programme, patients will be stimulated to develop an active lifestyle. An active lifestyle is defined as being moderate to highly physically active for at least 30 min a day, according to the World Cancer Research Fund/AICR, American Institute for Cancer Research (WCRF/AICR) guidelines for patients with cancer (www.aicr.org). If necessary, in consideration with the physiotherapist, patients will gradually increase their physical activity level during the first four weeks of the programme until they adhere to the WCRF/AICR guideline.

Patients will also be encouraged to reduce sedentary time during the day. Patients will receive a wristband, the Jawbone UP2™ (Jawbone, San Francisco, CA, USA), to track activity and raise awareness of their sedentary behaviour. The “Idle” alert will be used, i.e. the band gently vibrates when the patient has been inactive for a period of 45 minutes. Furthermore, the activity tracker and the accompanying Smart Coach application will be used to encourage an active lifestyle by, amongst others, setting personal step-goals per day and giving personalized feedback on patients’ activity levels.

To enhance adherence to the exercise programme and help patients to achieve and maintain an active lifestyle, physiotherapists are instructed to motivate patients according to the principles of Bandura’s social cognitive theory (SCT), i.e. enhancing self-efficacy by giving positive feedback on their progress and the starting point of the training schedule has been carefully chosen so it will be likely that the patient will succeed [29]. As a result, it is expected that patients develop a feeling of mastery (mastery experience).

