### Statistical analyses

#### Sample size calculation

The sample size calculation is based on the intention-to-treat analyses of the primary effectiveness outcome QoL (EORTC-QLQ-30) [30]. Here, we determine a clinically relevant difference as a difference of 10 points [30]. A difference of 10 points is realistic because in a previous exercise trial in patients with cancer, QoL in the intervention group improved by 15.1 points (SD 17.7) and in the control group by 6.1 points (SD 17.1) using the EORTC-QLQ-30 after the 12-week intervention [34, 35]. Therefore, using the control group data from the previous trial and the 10-point difference, we assume a 6-point increase in QoL in the control group and a 16-point increase in the intervention group, among patients who accept the intervention in this cmRCT. We expect an attendance rate of 70% in the intervention group and assume that the improvement in non-attenders randomized to the intervention group (30%) is equal to the improvement in the control group (i.e. 6 points). Furthermore, we assume that non-attendance does not impact the standard deviation. As a result, we estimate a mean improvement of 13 points in the intervention group ((70*16 + 30*6)/100 = 13) instead of 16 points and a mean improvement of 6 points in the control group. Using these numbers, standard deviations of 17.7 and 17.1, power of 80% and alpha of 0.05, we calculated that 98 patients are needed in each group.

As we will use linear regression analyses adjusted for baseline, the correlation between baseline and follow up needs to be taken into account in the sample size calculation. Therefore, the calculated number of subjects should be multiplied by (1-*ρ*
^2^), plus one extra subject per group [36], where *ρ* represents the correlation between baseline and follow-up outcomes. In our previous trials [34, 35], we identified correlation of 0.4 between baseline and follow-up QoL. This leads to a final sample size of 83 patients per group (98*0.84 + 1). As recommended by Candlish [37], we will update the sample-size calculation before the end of the trial when the actual acceptance rate of the intervention deviates from the estimated rate and adapt the sample size accordingly.

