#### Effectiveness outcomes

To assess differences in changes from baseline to 6 months in patient-related outcomes (QoL, fatigue, anxiety and depression and sedentary behaviour) between intervention and control, we will use intention-to-treat linear regression analyses adjusted for baseline. Mixed linear regression models adjusted for baseline will be used for the analyses of repeated outcomes (i.e. 6–24 months follow up).

The continuous within-group measurements in the intervention group, i.e. cardiorespiratory fitness, anthropometrics and patient-reported outcomes, will be analysed by the paired *t* test (if normally distributed) or Wilcoxon signed-rank test (if skewed).

From all UMBRELLA participants meeting the inclusion criteria for UMBRELLA Fit, we randomly selected patients for the intervention or control group with a 1:1 ratio. Besides comparison between patients in the intervention group and patients in the control group, we will investigate whether intervention effects change if we compare patients in the intervention group with all patients within UMBRELLA who are eligible for the UMBRELLA Fit study. Also, the timing of the regular measurements relative to the start and end of the intervention may vary between patients in the intervention group. Therefore, we will also assess QoL immediately at the start and end of the intervention. We will compare these outcome measures with the outcome measures from the regular UMBRELLA measurements completed before the start of the intervention and 6 months later (different and longer measurement intervals).

Patients may refuse the intervention after randomization and thus receive standard care. As a result, the estimated effect of the intervention may be diluted. We will conduct instrumental variable (IV) analyses [40, 41], taking non-compliance into account and assuming that the improvement in non-attenders randomized to the intervention group is equal to the improvement in the control group and that it does not impact the standard deviation. The IV method evaluates the effect of an intervention among “compliers”, who are individuals who would have received the intervention if it had been offered to them.

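### The instrumental-variable analysis has two definitions of compliance; if the one requiring completion sets the exposure and early stoppers benefit, the complier effect is overstated

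*Protocol article*

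**What the plan says.** Two parts of the protocol article describe the same IV analysis.

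- **Statistical analyses, Effectiveness outcomes.** The reason given for the analysis is refusal: "Patients may refuse the intervention after randomization and thus receive standard care". The analysis is to proceed "assuming that the improvement in non-attenders randomized to the intervention group is equal to the improvement in the control group". Compliers are defined as people who would take up the intervention on being offered it. Completion is not part of that definition.
- **Discussion.** The method is said to take drop-out as well as non-compliance into account. The stated difficulty is that "we only know who will accept and complete the exercise programme in the intervention group", with no such information for controls. The next sentence again contrasts patients who accept and finish with those who do not. A prognostic model is then promised, to predict from non-compliance in the intervention arm which controls would have complied.

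Three other sections bear on the point. Exercise intervention describes more than the supervised sessions: "In addition to the supervised exercise programme, patients will be stimulated to develop an active lifestyle". It adds an activity tracker and, where needed, a build-up of daily activity over the first four weeks. Adherence and compliance says the physiotherapist records attendance. Sample size calculation sets the planning values: "we assume a 6-point increase in QoL in the control group and a 16-point increase in the intervention group, among patients who accept the intervention", and "We expect an attendance rate of 70% in the intervention group".

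**The concern.** The two descriptions differ over one kind of patient: someone who accepts, trains for some weeks and then stops. Under Effectiveness outcomes this patient received the intervention and is a complier. Under the Discussion the patient did not complete and is a non-complier.

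The classification matters because the IV estimate rests on the assumption that the unexposed part of the intervention arm improves only as much as controls. That is plausible for refusers, who receive standard care. It is hard to defend for someone who had several weeks of supervised training, lifestyle encouragement and possibly the tracker. If such patients are coded as unexposed, whatever they gained is credited to the completers.

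The IV analysis is the plan's answer to the dilution it expects in this design. Two incompatible definitions also leave the choice open until after the data are seen. The problem does not depend on the prognostic model: it remains if the ITT difference is simply divided by the compliance proportion.

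**Working it through.** **Inputs**

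- Planned effect among acceptors: 16 − 6 = 10 points (Sample size calculation).
- Proportion of the intervention arm exposed: 70% (same section, which uses acceptance and attendance interchangeably). Assumption here: all who accept also start.
- SDs, power and alpha: "standard deviations of 17.7 and 17.1, power of 80% and alpha of 0.05"; baseline correlation 0.4. Patients are "randomly allocated to the intervention or control group with a 1:1 ratio".
- Completion among starters: median 87%, interquartile range 80% to 96%. The Methodological outcomes section quotes this from an external review as a comparator. It is not the trial's own planning value.
- Exposure in the control arm: 0, since controls are not offered the programme.
- Benefit in early stoppers, as a fraction f of the completers' effect: not given in the document. Assumption, shown from 0 to 1.

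**Reproducing the plan's figures**

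Diluted ITT effect: 0.70 × 10 = 7 points, that is 13 − 6.

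Pooled SD = √[(17.7² + 17.1²)/2] = 17.40. With two-sided alpha (sidedness is not stated), n = 2 × [17.40 × (1.960 + 0.842)/7]² = 97.02, rounded up to 98 per group. Then 98 × (1 − 0.4²) + 1 = 83.3, against 83 stated. Both figures reproduce. They depend on the 70% and the 10 points in acceptors, with no reference to completion.

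**The IV step**

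The simple (Wald) estimator is the ITT difference divided by the proportion classed as exposed in the intervention arm. Let c be completion among starters, completers gain 10 points and early stoppers gain 10f.

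- ITT = 0.70 × 10 × [c + f(1 − c)]
- Exposed = started: ITT/0.70 = 10 × [c + f(1 − c)]. This is the average effect in starters, whatever f is.
- Exposed = completed: ITT/(0.70c) = 10 × [1 + f(1 − c)/c]. The true effect in completers is 10, so the relative overstatement is f(1 − c)/c.

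| Completion c | Fraction f | ITT | Exposed = started | Exposed = completed | Overstatement of completer effect |
|---|---|---|---|---|---|
| 87% | 0 | 6.09 | 8.70 | 10.00 | 0% |
| 87% | 0.25 | 6.32 | 9.02 | 10.37 | 4% |
| 87% | 0.5 | 6.54 | 9.35 | 10.75 | 7% |
| 87% | 0.75 | 6.77 | 9.67 | 11.12 | 11% |
| 87% | 1 | 7.00 | 10.00 | 11.49 | 15% |
| 80% | 0.5 | 6.30 | 9.00 | 11.25 | 12.5% |
| 80% | 1 | 7.00 | 10.00 | 12.50 | 25% |
| 96% | 0.5 | 6.86 | 9.80 | 10.21 | 2% |
| 96% | 1 | 7.00 | 10.00 | 10.42 | 4% |

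The ITT effect equals the planned 7 points only when f = 1, because the plan gives every acceptor 10 points. In the other rows it is lower.

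For any given ITT result, the completion-based estimate exceeds the start-based one by a factor 1/c: 1.15 at 87%, 1.25 at 80% and 1.04 at 96%. Only f(1 − c)/c of this is bias. The rest reflects that the two estimates refer to different groups of patients.

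**The case against.** A reader might infer that the plan does code early stoppers as unexposed, and so will overstate the complier effect. The document does not support that.

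- No section fixes the coding of the exposure. The formal definition, in the analysis section, does not require completion and gives no such bias.
- The stated no-benefit assumption concerns non-attenders. Someone who trained for several weeks is not naturally a non-attender, so the analysis section already leans towards a split by attendance.
- The completion wording appears only in the Discussion, where it introduces the problem of missing information on controls. Drop-out after randomization could include refusal, because the offer follows randomization.

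All of this stands and makes the point conditional. It does not remove the contradiction. The Discussion is where the prognostic model is set out as planned work, and it twice describes the group by completion. An article may leave the coding of a variable to a fuller document, but here the article makes two statements that cannot both be followed.

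A reader might also infer that early stopping is expected to be common. The Background says only that less motivated patients may take part and that this might raise drop-out. The Discussion expects more drop-out than in conventional trials but does not separate refusal from stopping early.

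Finally, a definition based on starting is not free of assumptions. Consenters have the baseline assessment before training, and the document does not say when the tracker is handed out. Counting consenters who never attend as unexposed therefore assumes that they gain nothing.

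**Conclusion.** The concern holds in conditional form. The two descriptions of compliance are incompatible and must be reconciled. If the Discussion's wording sets the exposure and early stoppers gain any benefit, the no-benefit assumption fails for them and the complier effect is overstated.

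The size rests on two things that the trial does not fix: the benefit in stoppers, which is assumed, and the completion rate, which is borrowed from an external review. On those terms the overstatement is nil to 15% at 87% completion, with 25% as the upper end at 80% completion and full benefit. The IV analysis supplements the ITT analysis. The ITT result and the sample sizes of 98 and then 83 per group do not change.

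**What to change.** Use one exposure definition under Effectiveness outcomes, in the Discussion and in any prognostic model: started the programme, meaning attended at least one supervised session according to the physiotherapist's attendance records.

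- Count everyone who starts as exposed, whenever they stop.
- Count refusers, patients found ineligible at the last check and consenters who never attend as unexposed.
- Remove completion and drop-out from the description of the IV analysis.
- State that the estimate is the average effect in starters, and that it assumes consenters who never attend gain nothing.

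The cost is wording only, since attendance is already recorded. The small downside is that the estimate will look less favourable than one based on completers.

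### The protocol treats unknown compliance among controls as a gap in the instrumental-variable analysis and plans a prognostic model to fill it, although the complier effect needs no such data; its stated assumption and exposure also need restating.

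*Protocol article*

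**What the plan says.** Under Recruitment and allocation and under Control group, the protocol article says that controls are not told of the study and receive usual care. The exercise programme is offered only after randomisation, and only to the intervention group.

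Under Effectiveness outcomes, IV analyses are planned because patients may refuse the offer. They are to be done "assuming that the improvement in non-attenders randomized to the intervention group is equal to the improvement in the control group", with the further condition that the standard deviation is unaffected. Compliers are described there as people who would have received the intervention if offered it.

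The Discussion names random assignment as the instrument. It then lists as a disadvantage that acceptance and completion are known only in the intervention group, and adds: "Patients who accept and complete the exercise programme might differ from those who do not". As the remedy, "we will develop a prognostic model to estimate which patients would have been compliant in the control group", using the non-compliance seen in the intervention group.

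**The concern.** Three things look wrong.

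- **The prognostic model answers a problem that IV does not have.** With randomisation and no access to the programme for controls, the expected share of compliers is the same in both groups. The estimator needs only that share, not the identity of the control compliers. Predicting compliers from covariates adds the assumption that nothing unmeasured, such as motivation, drives both uptake and QoL. The instrument exists to avoid that assumption.
- **The stated assumption is not the IV condition.** IV needs the exclusion restriction: being offered the programme and not taking it up does not itself change the outcome. Equating non-attenders with the whole control group is stronger. It also sits uneasily with the Discussion's remark that acceptors might differ, and with the Background's report that refusers of exercise trials were older, more fatigued and had more comorbidity.
- **Exposure shifts** from not refusing (Effectiveness outcomes) to accepting and completing (Discussion). Under the second, people who attended part of the programme count as untreated, which breaches the exclusion restriction if partial attendance helps.

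The Discussion offers IV as its answer to dilution of the ITT effect, so this would be the trial's main estimate of benefit among those who take up exercise.

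**Working it through.** **Inputs, all from Sample size calculation.** "standard deviations of 17.7 and 17.1, power of 80% and alpha of 0.05"; "we assume a 6-point increase in QoL in the control group and a 16-point increase in the intervention group"; "We expect an attendance rate of 70% in the intervention group"; "we estimate a mean improvement of 13 points in the intervention group"; "we identified correlation of 0.4 between baseline and follow-up QoL".

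**The plan's own figures reproduce.** ITT difference = 13 − 6 = 7. Two-sided, n per group = (1.96 + 0.84)² × (17.7² + 17.1²)/7² = 97.02, or 97.99 with the t distribution; rounded up, 98 as stated. Then 98 × (1 − 0.4²) + 1 = 83.32, stated as 83.

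**Complier effect.** Wald estimate = ITT difference / acceptance in the intervention group = 7/0.70 = 10.0. This is the planned effect among acceptors, recovered without any compliance data from controls.

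**Is the stated assumption needed?** Hold the control mean at 6, acceptance at 70% and the complier effect at 10. Let non-attenders improve by m. Compliers left untreated would then improve by c = (6 − 0.3m)/0.7, and the ITT difference is 0.7(c + 10) + 0.3m − 6 = 7 for every m.

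| m | c | Wald estimate | Attenders minus all controls (c + 10 − 6) |
|---|---|---|---|
| 0 | 8.57 | 10.0 | 12.6 |
| 3 | 7.29 | 10.0 | 11.3 |
| 6 | 6.00 | 10.0 | 10.0 |
| 9 | 4.71 | 10.0 | 8.7 |
| 12 | 3.43 | 10.0 | 7.4 |

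The assumption matters only for the direct contrast in the last column, not for the IV estimate.

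**If predictions select or weight controls.** Simulation with 83 per group, 1,500 runs, about 70% acceptance and a true effect of 10. Covariate strengths are assumed, as the article gives none. Observed acceptors are compared with controls weighted by predicted compliance, or with controls classified as compliers. Entries are mean (empirical SD).

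| Drivers of both uptake and QoL | Wald | Weighted | Classified |
|---|---|---|---|
| None | 10.05 (3.87) | 10.06 (3.02) | 10.11 (3.22) |
| Measured only | 9.92 (3.78) | 9.91 (2.91) | 8.96 (3.14) |
| Measured and unmeasured | 9.89 (3.95) | 10.86 (2.97) | 9.79 (3.19) |
| Unmeasured only | 9.99 (3.95) | 10.93 (3.04) | 10.92 (3.22) |
| Unmeasured only, stronger | 9.95 (3.85) | 11.75 (2.92) | 11.76 (3.18) |

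The Wald SD is larger by 20% (3.87/3.22) to 33% (3.95/2.97).

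**Exposure definition.** Methodological outcomes cites an 87% completion rate from an external review. Suppose it applied on top of 70% acceptance, completers gain 10 points, and partial attenders gain a fraction f of that. The ITT difference is 0.70 × 10 × (0.87 + 0.13f). Dividing by the completer share, 0.70 × 0.87 = 0.609, gives 10(0.87 + 0.13f)/0.87: 10.0 at f = 0, 10.7 at f = 0.5 and 11.5 at f = 1. Dividing by 0.70 instead gives 10(0.87 + 0.13f), from 8.7 to 10.0, which is the average effect of starting the programme.

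**The case against.** A reader might infer that the trial will replace its randomisation-based estimate with a confounded one. The text does not support that. It keeps assignment as the instrument, defines compliers correctly under Effectiveness outcomes, and never says how the predictions enter an estimator. The model could serve only to describe compliers. This part of the objection stands.

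A reader might also infer that the assumption under Effectiveness outcomes invalidates the IV result. It does not: the first table shows the Wald estimate unmoved. The wording may be a loose statement of the exclusion restriction carried over from the sample size section. Nor is the clash with the Discussion a formal contradiction, since acceptors can differ in age or comorbidity without differing in mean improvement.

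The figure of 11.5 is a worst case. It needs partial attenders to gain the full effect, the 87% is not a planning value for this trial, and the 70% attendance rate may already exclude some non-completers.

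The simulated bias depends on chosen strengths and is modest beside a Wald SD of 3.8 to 4.0. Even in the last scenario the weighted contrast has the smaller root mean squared error: √(1.75² + 2.92²) = 3.4 against about 3.85. What this does not answer is that such bias cannot be checked from the data, does not shrink with sample size, and is not reflected in the interval.

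Nothing in the objection rescues the claim that IV lacks something for want of control compliance data.

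**Conclusion.** The Discussion is wrong to present unknown compliance among controls as a limitation of IV in this design. The complier effect is 7/0.70 = 10.0 on the plan's figures and needs only the two group means and the intervention-group acceptance rate. This rests on randomisation, on controls having no access to the trial programme, and on the exclusion restriction for those who do not take it up.

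Harm from the prognostic model is conditional. If predictions select or weight controls, the estimate can move either way, from 9.0 to 11.8 around 10 in the assumed scenarios. The stated assumption should be replaced because it is unnecessary and in tension with the Discussion, not because it biases the IV estimate. The double definition of exposure could inflate the result from 10.0 up to 11.5 if the cited completion rate applied.

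This concerns a supplementary analysis. The ITT analysis and the sample sizes of 98 and 83 per group stand.

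**What to change.** - Define exposure once: having started the programme (at least one session) before the outcome questionnaire. This also settles how to count late starters and those screened out after randomisation.
- Estimate the complier effect by two-stage least squares, with randomised group as instrument and baseline QoL and the randomisation stratum (12 or 18 months since enrolment) as covariates.
- Replace the assumption under Effectiveness outcomes with the exclusion restriction: for those who do not start, being offered the programme has no effect on the outcome. Drop the standard-deviation condition.
- Remove the Discussion's statement that compliance data are lacking for controls. Keep the prognostic model only to describe acceptors, or as a sensitivity analysis labelled as resting on no unmeasured confounding.

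The cost is wording. No data collection changes. There are two downsides. The interval will be wider than that of a model-based contrast, by roughly 20 to 33% in the assumed simulations, which did not adjust for baseline. And the result is the effect of starting the programme, averaged over completers and partial attenders, which should be said when it is reported.
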